## **5.7    Unscheduled Visits**

Participants will encounter at the clinic and have unscheduled visit for any reasons. They will be asked to answer questions in Module 1 or Module 2 according to their assignment. They will also undergo three mandatory assessments, including **best-corrected visual acuity testing, slit-lamp biomicroscopy and ophthalmoscopy**, and other examinations at investigator's discretion. For those with disease worsening, participants will receive best medical judgment and proper treatment for worsening of the ocular or systemic conditions.

## **5.8    Withdrawn and Lost to Follow-up**

Subjects have the right to withdraw from the trial at any time and for any reason, without providing a reason. The investigator has the right to withdraw participants from the study and abandon assigned intervention strategies in the event of inter-current illness, adverse events, protocol violations or other reasons.

If the subject withdraws from the trial, efforts will be made to continue to obtain follow-up data, with the permission of the subject. They will be given appropriate treatment, but will not continue with scheduled study follow-ups unless they allow it.

Subjects will also be considered to have been withdrawn if they declare they are no longer interested in further participation, or have died. If the death is considered to be related to the vaccines, the subject will be declared serious adverse event, rather than withdrawn.

Missing a phone call or visit does not necessarily mean that a patient has been withdrawn from the study. For these subjects, efforts will be made to contact them and bring them back as soon as possible.

For those subjects fail to response the contact or to attend study visits without stating

an intention to withdraw from the study, the Investigator should contact the subject through telephone calls as soon as possible. The investigator will attempt to contact them for at least three times at each scheduled visit. If contact cannot be established up to the end of the trial, the subject should be considered as “lost to follow-up” on the date of last contact.

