# **1 Introduction**

This is an investigator-initiated, parallel group-randomized, pragmatic trial to test the difference in ocular and systemic outcomes between prompt initiation of COVID-19 vaccination and deferred initiation of COVID-19 vaccination in patients with uveitis.

Approximately 1314 eligible subjects will be randomized 1:1 (657 subjects per group) to receive one of two vaccination strategy recommendations. In the prompt vaccination arm, subjects will be recommended to get a prompt initiation of COVID-19 vaccination. In the deferred vaccination arm, subjects will be recommended to get the vaccination after uveitis remission (inactive disease for 3 months after discontinuing all treatments for eye disease). All participants will be followed up for 3 months since randomization. The primary outcome will be the difference in time to symptomatic uveitis worsening.

The statistical analysis plan (SAP) documents the planned statistical analyses for the trial and is based on the protocol, together with any subsequent amendments. The SAP is intended for the use of project team members and should be read in conjunction with the aforementioned protocol. The analyses that are detailed in this SAP will be performed only when the database has been locked and all protocol violators identified. Analysis populations will be determined using the rules prespecified in this SAP. At a date to be agreed within the project team, a data look and further analysis will be performed.

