## **5 Sample Size**

A two-sided log-rank test with an overall sample size of 1314 subjects (657 in the deferred vaccination group and 657 in the prompt vaccination group) achieves 80.0% power at a 0.050 significance level to detect a hazard ratio of 1.5 when the proportion surviving (no occurrence of symptomatic uveitis worsening) in the deferred vaccination group is 0.9000. The study lasts for 6 time periods of which subject accrual (entry) occurs in the first 3 time periods. The accrual pattern across time periods is uniform (all periods equal). The proportion dropping out of both groups is 0.1500, respectively.

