## **7 Analysis Population**

### **7.1 Intention-To-Treat Population**

The Intent-To-Treat (ITT) Population will consist of all patients who have undergone randomization in the study regardless of their compliance with the study assignment. For all ITT analyses, participants will be analyzed as randomized.

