## **8 Missing Data**

For baseline characteristics, missing values will be expected to be rare, and will not be imputed. In the primary analysis, the follow-up data will be censored at the follow-up encounter reporting the occurrence of primary endpoint event, withdrawal or loss to follow-up, or the final (month 3) visit (whichever is earlier). There is plan to impute missing data for those who withdraw or are lost to telephone follow up before month 3 with the use of multiple imputation in a sensitivity analysis. Analyses on secondary outcomes will be performed without data imputation.

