## **10 Primary Outcome Comparison**

The primary outcome, time to uveitis symptomatic worsening over the course of 3 months of follow-up, will be compared with the Log-rank test. If a participant does not experience the primary endpoint event, they will have their data censored at the encounter where withdrawal or loss to follow-up occurs, or the final (month 3) follow-up encounter (whichever is earlier). For those with primary endpoint event, the censoring time point will be at the specific telephone call encounter (month 1, month 2, or month 3) where the occurrence of primary endpoint event is reported. Follow-up data after month 3 will no longer be included in the analysis, if any. The multiplicative limit method (Kaplan-Meier) will be used to show the cumulative incidence of primary endpoint event. A proportional hazard model (univariate Cox regression) is used to calculate the hazard ratio as well as 95% CI. The proportional-hazards assumption will be checked by means of inspection of a log-log survival plot.

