## **13 Sensitivity Analysis Evaluating Non-Response**

It is expected that there will be missing data on the primary outcome status for those who withdraw or are lost to follow-up before the final month 3 follow-up encounter. It is assumed that the missing data will be missing completely at random. The multiple imputation will be employed to predict the missing status (occurrence of the primary endpoint event or not) of those participants when outcome data are missing. This analysis includes all ITT population. It is planned to predict the missing values in 20

imputation datasets based on all available baseline clinical characteristics, treatment assignment and completed follow-up encounters. The imputed outcome will be analyzed in each imputation dataset with the Cox regression model as it is performed in the primary analysis. With the use of the Rubin's rules, the results of the imputations will be combined to get a final answer that takes into consideration of the variability in the datasets.

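### SAP section 8 ends primary follow-up at withdrawal although protocol 5.8 keeps seeking data afterwards, and SAP section 10 does not agree with it on how such data are used

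*Supplement*

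**What the plan says.** Protocol version 2.0, section 5.8, lets the subject withdraw at any time. It also lets the investigator withdraw a subject and abandon the assigned strategy for inter-current illness, adverse events, protocol violations or other reasons. Data collection need not stop there: "If the subject withdraws from the trial, efforts will be made to continue to obtain follow-up data, with the permission of the subject". Scheduled follow-ups stop by default but may go on if the subject allows it.

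The SAP handles withdrawal in four places.

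- **Section 7.1** defines the ITT population as "all patients who have undergone randomization in the study regardless of their compliance with the study assignment", analysed as randomized.
- **Section 8** gives the censoring rule for the primary outcome: "the follow-up data will be censored at the follow-up encounter reporting the occurrence of primary endpoint event, withdrawal or loss to follow-up". The month 3 visit is a further cut-off, and the earliest of these applies.
- **Section 10** says of participants who do not have the primary event that "they will have their data censored at the encounter where withdrawal or loss to follow-up occurs", or at month 3 if earlier. Participants with an event are timed at the month 1, 2 or 3 call that reports it. Only data after month 3 are excluded outright.
- **Section 13** expects that "there will be missing data on the primary outcome status for those who withdraw or are lost to follow-up" before month 3. It imputes event status where outcome data are missing, under missing completely at random, as a sensitivity analysis.

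Neither document says that primary-outcome data obtained after a withdrawal are used.

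**The concern.** In protocol 5.8 a withdrawn participant may still be answering symptom calls. In SAP section 8 withdrawal closes the record for the primary analysis. If section 8 is followed, outcome information that the protocol tries to obtain is not used in the log-rank test or the Cox model.

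Two things are at stake. The first is precision, since events and person-time are lost. The second is bias. The listed grounds for investigator withdrawal include adverse events and protocol violations, and the treating ophthalmologist knows the assignment. Withdrawal could therefore differ by arm and be related to the eye outcome. Censoring at withdrawal would then be informative even where later follow-up could have removed the problem.

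**Working it through.** **Step 1: the rules applied to two participants.** Both are withdrawn at Month 1 and permit further calls.

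| | Reports 3 days of eye pain at Month 2 | No symptoms through Month 3 |
|---|---|---|
| SAP 8 | censored at Month 1 | censored at Month 1 |
| SAP 10, read literally | event at Month 2 | censored at Month 1 |
| All data under protocol 5.8 | event at Month 2 | censored at Month 3 |

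Sections 8 and 10 disagree on the first participant. Neither uses the full record of both.

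**Step 2: the plan's sample size.** SAP section 5: "A two-sided log-rank test with an overall sample size of 1314 subjects" that "achieves 80.0% power at a 0.050 significance level to detect a hazard ratio of 1.5", with event-free proportion 0.90 in the deferred arm, uniform accrual over 3 of 6 periods, and 15% dropout. The time point of the 0.90 is not stated; I assume 3 periods.

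- Freedman events: ((1 + 1.5)/(1.5 − 1))² × (1.960 + 0.842)² = 25 × 7.85 ≈ 196.2, so 197.
- Hazards: λ₀ = −ln(0.9)/3 = 0.0351 and λ₁ = 1.5 × λ₀ = 0.0527 per period. The mean event probability over 3 to 6 periods of follow-up is (0.146 + 0.210)/2 = 0.178.
- N = 197/0.178 ≈ 1107, and 1107/0.85 ≈ 1303, which is 0.8% below 1314.

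The stated figure reproduces and is not in dispute here.

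**Step 3: events at stake if withdrawal is non-informative.** Follow-up is 3 months with 657 per arm.

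- Complete follow-up: 657 × [0.100 + (1 − 0.9^1.5)] = 657 × (0.100 + 0.146) ≈ 161.7 events.
- Exponential dropout reaching 15% at month 3: η = −ln(0.85)/3 = 0.0542. Expected events per arm are 657 × λ/(λ + η) × (1 − e^(−3(λ+η))), which gives 657 × (0.0924 + 0.1352) ≈ 149.6.
- Difference: about 12 events (7.5%), if all dropouts are withdrawals who permit contact. With one third to one half permitting, it is about 4 to 6. If all dropout came straight after baseline, the limit is 0.15 × 161.7 ≈ 24.
- Cross-check with 5% withdrawn per arm, half at Month 1 and half at Month 2, all permitting: 32.85 × (0.0488 + 0.0705) ≈ 4 events.
- Schoenfeld power, Φ(√D/2 × ln 1.5 − 1.96): 69.8% with 149.6 events and 73.2% with 161.7. Both lie below 80% because step 2 credits 3 to 6 periods of follow-up while the analysis stops at month 3. That is a separate matter.

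**Step 4: informative withdrawal.** Simulation of 657 per arm with 600 replicates, true HR 1.5 before withdrawal, monthly assessments, Cox model with Efron ties, withdrawal at Month 1 or 2, and all permitting contact. The withdrawal rates and hazard changes are assumptions.

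| Withdrawn, prompt / deferred | Hazard after withdrawal | HR, all data | HR, censored |
|---|---|---|---|
| 15% / 15% | unchanged | 1.51 | 1.51 |
| 15% / 15% | doubled in both arms | 1.50 | 1.50 |
| 15% / 15% | doubled, prompt only | 1.61 | 1.51 |
| 15% / 15% | tripled, prompt only | 1.69 | 1.49 |
| 20% / 10% | doubled, prompt only | 1.64 | 1.49 |

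SE(log HR) at about 150 events is 2/√150 ≈ 0.163. The simulation error of a mean is then 0.163/√600 ≈ 0.007, or about 0.01 on the HR, so every censored value is 1.50 within noise. The shift in the third row is ln(1.61/1.51) ≈ 0.064, about 0.4 SE. In the fourth it is ln(1.69/1.49) ≈ 0.126, about 0.8 SE.

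**Step 5: the literal reading of SAP 10.** It counts late events but drops late event-free time. Suppose there is no true effect, the hazard is unchanged by withdrawal, and 20% against 10% withdraw at Month 1 or 2 (on average half of the 3 months remaining). About 10% and 5% of person-time are lost and no events. The rate ratio becomes roughly 0.95/0.90 ≈ 1.06 instead of 1.00. With equal withdrawal the distortion largely cancels in the ratio, though both arms' rates are overstated.

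**The case against.** The strongest counter-case is that only one sentence, in SAP section 8, clearly puts withdrawal ahead of a later event. A reader might infer more than the text supports in four ways.

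- **That sections 8 and 10 both delete post-withdrawal events.** Section 10's withdrawal clause is limited to participants without the primary event, and its next sentence times events at the reporting call. Read literally it counts such an event. This stands. What remains against section 10 is the loss of event-free time and the conflict with section 8.
- **That section 13 imputes over observed outcomes.** Its imputation applies when outcome data are missing, and a recorded event is not missing. This stands too. The section is merely silent on whether post-withdrawal status is used.
- **That the data already exist and events are certainly lost.** A loss needs a withdrawal, permission, a completed symptom assessment and, for an event, onset reported by month 3. The documents give no rate for any of these, and the 15% dropout is not split between withdrawal and loss to follow-up.
- **That the analysis ceases to be ITT.** Withdrawn participants stay in the population, in their assigned arm, and withdrawal is not the same as non-compliance. Under protocol 5.6 a deferred-arm patient vaccinated before remission continues to be observed. The shortfall is in follow-up, not in who is included.

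It could also be said that withdrawal in the SAP means withdrawal from all follow-up. The SAP does not define it so and asks to be read with the protocol, where 5.8 uses the term more widely.

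**Conclusion.** The point holds as a defect in the censoring rule. SAP section 8, as written, discards any event or event-free time observed between withdrawal and month 3. Section 10 gives a different rule that is itself unbalanced. The two need reconciling with each other and with protocol 5.8.

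The size is conditional. If withdrawal is non-informative, the HR does not move. The cost is about 4 events (5% withdrawn per arm) to 12 events (all 15% dropout treated as withdrawal) out of about 162, and at most about 3 power points. It shrinks in proportion to the share who permit contact. If withdrawal is informative and acts differently in the two arms, the HR can shift, for example 1.61 with all data against 1.51 censored. That example assumes a post-withdrawal hazard doubled in the prompt arm only and full permission, neither of which comes from the documents. Raising the hazard equally in both arms, with equal withdrawal, left the HR unchanged. The illustrated shifts are below one standard error, so this is a correction worth making before database lock and not evidence that the primary result would be wrong.

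**What to change.** 1. **SAP sections 8 and 10:** use one rule in both. Count events and event-free time observed up to month 3, whether before or after withdrawal from the assigned strategy. End follow-up at withdrawal only when the participant refuses further contact.
2. **Other event-free participants:** censor at the last symptom assessment up to which symptom history is continuously covered. The telephone questions ask only about the past month, so a later call after a missed month does not show that the missed month was event-free. Either ask about the whole interval since last contact, or censor at the start of the gap.
3. **SAP section 13:** state that observed post-withdrawal status is used and that only unobserved status is imputed.
4. **Reporting:** in the CONSORT diagram, show by arm how many withdrew from the strategy only and how many refused further contact.

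The cost is SAP wording plus, if the first option in item 2 is chosen, a small change to the telephone script. Protocol 5.8 already seeks the data, so no extra visits or participants are needed.

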## **5.5 Interventions**

Interventions will take place at the Baseline visit. The Primary Treating Ophthalmologist will provide the recommendation of COVID-19 vaccination to the subject according to randomization assignment. For those randomized to the prompt vaccination, subjects will be recommended to go to vaccination site and get COVID-19 vaccination as soon as possible. Our ophthalmologic clinic does not provide the vaccination service. We will only give the recommendation to patients. For those randomized to the deferred vaccination, subjects will be recommended to get COVID-19 vaccination after the remission of uveitis. **Remission is defined as an inactive disease for 3 months after discontinuing all treatments for eye disease.** At baseline, all patients will also be educated to immediately contact us by phone call once they experience any discomfort or have any new ocular symptoms of eye redness, eye pain, decreased vision, light sensitivity or fark, floating spots. We will ask questions as prespecified in **5.6 Follow-up** on the phone call.

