## **7 Adverse Events**

### **7.1 Adverse Event Reporting**

An adverse event (AE) is defined as any unfavorable medical occurrence in a subject who has ever received study intervention, regardless of a causal relationship with this intervention. Any worsening of a pre-existing condition or illness should be considered an adverse event. Worsening in severity of a reported adverse event should also be reported as a new adverse event. An elective surgery/procedure scheduled to occur during a study will not be considered an adverse event if the surgery/procedure is being performed for a pre-existing condition and the surgery/procedure has been pre-planned prior to study entry. However, if the pre-existing condition deteriorates unexpectedly during the study (e.g., surgery performed earlier than planned), then, the deterioration of the condition for which the elective surgery/procedure is being done will be considered an adverse event. For adverse events to be considered intermittent, the events must be of similar nature and severity.

The Investigator will monitor each subject for clinical and laboratory evidence of adverse events throughout the study. The Investigator will assess and record any adverse event in detail including the date of onset, event diagnosis (if known) or sign/symptom, severity, time course, duration and outcome, relationship of the adverse event to study intervention and any actions taken. All these information on non-serious and serious adverse events will be recorded at each study visit.

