### **7.2 Serious Adverse Events**

Serious adverse events (SAE) should be reported to Chief Investigator and Ethics Committee within 24 hours of the Investigator being made aware of the SAE. Serious adverse events include any medical occurrence that results in the following outcomes:

Death.

Life-threatening experience.

Non-elective surgery or hospitalization for any reason.

Congenital anomaly or birth defect.

Persistent or significant disability or incapacity.

Any other important medical events, not immediately life-threatening or resulting in death or hospitalization but requiring medical or surgical intervention to prevent serious outcome.

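### Protocol section 5.8 counts a death as a withdrawal unless it is judged vaccine-related, which contradicts sections 7.1 and 7.2, and the SAP has no rule for deaths

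*Supplement*

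**What the plan says.** Protocol 2.0, section 5.8, sets the default: "Subjects will also be considered to have been withdrawn if they declare they are no longer interested in further participation, or have died". The next sentence gives the only exception: "If the death is considered to be related to the vaccines, the subject will be declared serious adverse event, rather than withdrawn".

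The safety sections use a different rule. Section 7.1 defines an adverse event as "any unfavorable medical occurrence in a subject who has ever received study intervention, regardless of a causal relationship with this intervention". Section 7.2 opens its list with "Serious adverse events include any medical occurrence that results in the following outcomes", puts death first, attaches no relatedness condition, and requires a report to the Chief Investigator and the Ethics Committee within 24 hours of the Investigator's learning of the event. Section 7.4 makes causality a separate assessment of an adverse event, on three levels.

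The SAP does not mention death. Sections 8 and 10 censor event-free patients at withdrawal, loss to follow-up or the month 3 encounter. Section 13 plans multiple imputation for "missing data on the primary outcome status for those who withdraw or are lost to follow-up before the final month 3 follow-up encounter".

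**The concern.** Section 5.8 makes withdrawal and SAE alternatives for a death and chooses between them on relatedness to the vaccine. In this trial exposure to the vaccine is what the two strategies are meant to change, so a rule that depends on it can act differently in the two arms. Relatedness is judged by the Investigator, and the treating ophthalmologist is not masked.

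At stake is whether deaths are counted evenly. The trial weighs the ocular risk of prompt vaccination against leaving patients unvaccinated for longer, and a death while unvaccinated, including one from COVID-19, belongs on the second side of that balance. Few other routes would pick it up. All-cause death is not a listed outcome, no interim analysis is planned, and RT-PCR testing is specified for hospitalized cases, so a COVID-19 death outside hospital might reach neither the SAE log nor the laboratory-confirmed COVID-19 outcome.

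**Working it through.** The plan states no figure that can be reproduced here. The check sets the passages side by side.

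**Step 1: who is covered by sections 7.1 and 7.2.** The study intervention is advice, given in both arms at Baseline. Section 5.5 says of the clinic: "We will only give the recommendation to patients". An unvaccinated deferred-arm patient has therefore received the study intervention and falls under 7.1 and 7.2.

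**Step 2: how each kind of death is classified.**

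| Death | Section 5.8 | Sections 7.1 and 7.2 |
|---|---|---|
| Unvaccinated patient, either arm | Withdrawn | SAE |
| Vaccinated, judged unrelated or undeterminable | Withdrawn | SAE |
| Vaccinated, judged related | SAE, not withdrawn | SAE |

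The first row follows because a patient who has had no vaccine cannot have a vaccine-related death. The sections agree only in the last row.

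**Step 3: where unvaccinated patients will be.** Deferred-arm advice is that "subjects will be recommended to get COVID-19 vaccination after the remission of uveitis". Remission requires 3 months of inactive disease off all eye treatment, patients already in remission are excluded (section 4.2), and follow-up is 3 months (section 3.1). Most adherent deferred-arm patients would be unvaccinated for most or all of follow-up. This is not absolute: someone already off treatment for some weeks at entry could reach remission during follow-up, and section 5.6 foresees deferred-arm patients who are vaccinated early.

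**Step 4: what share of deaths section 5.8 alone would capture as SAEs.** Among unvaccinated patients, 0%. Among vaccinated patients, anything from 0% to 100%, depending on attribution. If attribution is 0%, the arms do not differ.

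**Step 5: what the SAP does with them.** A death labelled as a withdrawal is censored under SAP 8 and 10. Under SAP 13 the patient's month 3 status is then imputed in 20 datasets, assuming data missing completely at random. A death judged vaccine-related is by 5.8 not a withdrawal. It is not a loss to follow-up either, so it fits no stated censoring category.

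**Step 6: scale.** With 657 patients per arm, one death is 1/657 = 0.15% of an arm. The sample size section allows 15% dropout, or 657 × 0.15 = 98.55, about 99 patients per arm. A handful of deaths would hardly affect the primary analysis, and would be hard to see if pooled with about 99 dropouts.

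**The case against.** The strongest defence is that 5.8 deals with participant status and section 7 with safety reporting. Section 5.8 mentions neither the 24-hour report nor the Ethics Committee, and 7.2 already gives an unconditional rule that covers both arms. On that view withdrawal is only a disposition label that can stand beside an SAE. This does not remove the conflict. If every death were an SAE anyway, the exception for vaccine-related deaths would have nothing to do, and its wording sets the two labels against each other. Section 5.8 is also the place that says how a participant who dies is to be classified, so staff could reasonably take it as the specific rule.

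Other parts of the defence stand and limit the point. A reader might infer that deferred-arm deaths can never be SAEs, or that the Ethics Committee would not hear of them. The documents do not support that. A site applying 7.2 would report them, and a patient first hospitalized or in a life-threatening state already qualifies under criteria that 5.8 leaves alone. Time to hospitalization and time to laboratory-confirmed COVID-19 are secondary outcomes in any case.

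A reader might also infer a bias of certain direction against prompt vaccination. Step 4 shows why that goes too far: the difference depends on attribution and on actual vaccination, and unvaccinated prompt-arm patients are caught by the same rule. Nor is there a planned test to be biased. The SAP describes the incidence of systemic adverse events, and section 11.1 plans no formal comparison of secondary outcomes.

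**Conclusion.** The contradiction is real, stands in the current protocol, and nothing in the protocol or SAP resolves it. Followed as written, 5.8 leaves out of the SAE log any death in an unvaccinated patient and any vaccinated patient's death not judged related, unless an earlier event already qualified. That could make death reporting differ between arms. A shortfall in the deferred arm is the likelier direction, provided that deferred-arm patients mostly stay unvaccinated and that some deaths after vaccination are attributed to the vaccine.

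The number of deaths is unknown, because the documents give no rate, and over 3 months it is probably small. The primary hazard ratio is unlikely to move, since event-free deaths are to be censored either way. The SAP defect is confined mainly to the sensitivity analysis, where imputing eye symptoms after death has no sensible meaning. The case for correction rests on complete and even reporting of deaths.

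**What to change.** - **Protocol 5.8:** remove the causality condition. Record death as its own disposition category, separate from SAE status, and state that every death in either arm is an SAE, as 7.2 already provides. Causality is then assessed under 7.4.
- **Protocol 7.7:** this section says that an SAE leads without exception to immediate discontinuation of the study. Sections 5.8, 7.2 and 7.7 must be reconciled together, because clarifying which deaths are SAEs also decides when that sentence applies. What the sentence should say is for the investigators and the Ethics Committee.
- **SAP 8 and 10:** censor event-free patients who die at death, whatever the attributed cause. Because the SAP times events by monthly encounter, this shifts the censoring time by about one interval at most.
- **SAP 13:** do not impute status after death.
- **Reporting:** tabulate all-cause deaths by arm, and show them as deaths in the CONSORT flow diagram planned in SAP 9.

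The cost is a short protocol amendment, a few lines in the SAP, and possibly a few more SAE reports. No additional data are needed. The wording of 7.7 is the one item that needs discussion.
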